### Trial management

A TMG and an independent TSC have been assembled to monitor progress and provide advice. The TSC has agreed to play the role of a data monitoring committee. The TMG is composed of the PI, co-investigators and the SWELL research team at the Wolfson Centre and the Centre for Trials Research. The TSC comprises external experts on trials involving YP’s mental health, an independent statistician, a young person and a parent with lived experience of depression.

### Monitoring adverse events and safety protocol

In the YP eligible for this study, there is an inherent risk of self-harm and suicide. We have therefore defined expected adverse events *a priori* as suicidal thoughts with a plan, self-harm or suicide attempts. These adverse events are not expected to be related to the intervention, but the additional contact with the study team for YP in the intervention arm may create greater opportunity for reporting adverse events. Adverse events reporting procedures will be followed by all researchers working on the trial. A standard study procedure for documenting and dealing appropriately with these events will be followed. This includes risk assessment, signposting to services and liaison with clinical services as needed (see online supplemental material 5 for procedure).

## Discussion

This is a large-scale RCT to examine the effectiveness of an evidence-based group CBT intervention, adapted for online delivery with an added parent treatment phase to prevent the onset of MDD in YP. Treatment optimisation will be offered for parents who have elevated depressive symptoms at study entry to improve the effectiveness of the intervention for the YP. Although an intergenerational intervention, it involves working separately with parents and YP to improve their mental health, an approach that is consistent with current UK systems for supporting mental health. An embedded process evaluation will investigate the impact of this key adaptation.

This study will also evaluate the mechanisms through which the intervention has its effect using hypothesis-driven quantitative methods as well as exploratory qualitative methods, providing important insights into how intergenerational interventions might work to prevent depression in YP.

The source intervention for YP has been shortened and will be delivered entirely online by therapists at a level equivalent to those working with low-intensity psychological interventions in the NHS, making it a much-needed,^12^ scalable prevention programme for depression, if found to be effective.

### Ethics and dissemination

Ethical approval was granted by Wales NHS Research Ethics Committee 5 ([contact]) before the trial commenced (IRAS 305331; REC 22/WA/0254). This manuscript is based on V.5.7 of the protocol dated 17 January 2025. Significant protocol modifications will be communicated by submitting an amendment for ethical review and updating trial registry details. We will share deidentified individual participant-level data following publication of the main trial results on Cardiff University’s research data repository. We will follow BMJ regulations on authorship. Trial results will be published in peer-reviewed journals.

### Trial status

Recruitment started on 21 August 2023, the first participant was consented on 19 September 2023 and 267 participants had been recruited by 02 June 2025. Recruitment is planned to be completed by August 2025 with analysis and dissemination between September 2025 and February 2027. Cardiff University is the study sponsor (ref: SPON1902-22) and the study contact for enquiries is [contact].

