**Exclusion criteria**
Young person is already receiving specialist treatment for depression (eg, currently on antidepressants or receiving CBT).Young person has a current diagnosis of depression from a doctor or healthcare professional.A young person has been told by a doctor or healthcare professional that they have a diagnosis of bipolar disorder, schizophrenia, psychosis, eating disorder or alcohol/drug dependence.A young person has generalised learning difficulties that, the parent judges, would prevent them from participating in trial activities.Parent has a diagnosis of bipolar disorder, schizophrenia or personality disorder.Parent is receiving treatment from secondary mental health services (eg, community mental health team or psychiatrist).Parent or young person not resident in the UK.

At study enrolment, if the parent is currently depressed at the screening stage, they will be offered PTO. Baseline assessments will follow completion of PTO (or immediately if the parent refuses the PTO offer), and the YP will be randomised.

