### Sample size

We aim to recruit 400 YP and parents/carers, based on a previous study^17^ and sample size calculations. We allow for 10% loss to follow-up based on previous studies of this population and depressed YP.^1630^,^32^ The effect size observed in the study by Garber *et al*^16^ was a HR of 0.63. We expect the effect of the intervention in this RCT to be slightly greater than this due to the addition of PTO before randomisation. We therefore define the minimum clinically important difference for this study as an HR of at least 0.60 (equivalent to an 11% difference in MDD between study arms). With a sample size of up to 400 randomised participants, we estimate statistical power as 79.9% to detect a difference of at least HR=0.60 between study arms, with an assumed 10% attrition rate at 9 months, expected event rate probabilities at follow-up of 0.327 (control) and 0.211 (intervention) based on^17^ a one-sided alpha of 0.05. A HR of 0.56 (equivalent to a 12% difference between study arms) will attain 87.0% power. A STATA V.17 programme was used for this estimation.^33^

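### The reported accrual and August 2025 close point to about 292–306 participants, not the 400 on which the stated 79.9% and 87.0% power rest

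*Protocol article*

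**What the plan says.** The Sample size section of the protocol article sets the target: "We aim to recruit 400 YP and parents/carers". The power claim is tied to that number: "With a sample size of up to 400 randomised participants, we estimate statistical power as 79.9% to detect a difference of at least HR=0.60". It assumes 10% attrition at 9 months, event probabilities of 0.327 (control) and 0.211 (intervention), and "a one-sided alpha of 0.05". A second scenario follows: "A HR of 0.56 (equivalent to a 12% difference between study arms) will attain 87.0% power". No power is given for fewer than 400.

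The Trial status section says that recruitment opened on 21 August 2023 and that the first consent was on 19 September 2023. It then reports that "267 participants had been recruited by 02 June 2025. Recruitment is planned to be completed by August 2025". Analysis and dissemination run from September 2025 to February 2027.

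Enrolment and randomisation are separate steps. For families where the parent is depressed at screening, Box 1 states: "Baseline assessments will follow completion of PTO (or immediately if the parent refuses the PTO offer), and the YP will be randomised". Parent treatment optimisation (PTO) can last up to 12 weeks, and the Interventions section expects 40% of parents to meet its threshold.

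**The concern.** The two sections do not fit together. One gives power for 400 randomised; the other gives a count and a closing date that fall well short of 400 unless accrual rises several-fold in the last two to three months. The article neither comments on the gap nor says what power remains.

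The printed power is what tells a reader how far a non-significant result counts against an effect of HR 0.60, which the protocol names as its minimum clinically important difference. If the number randomised is nearer 300, the type II error at that difference is about 30%, not the 20% implied. A reader relying on the printed figure would give a null result more weight than the design supports.

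**Working it through.** **Inputs.** From Sample size: N = 400, attrition 10%, control risk 0.327, HR 0.60 or 0.56, one-sided alpha 0.05 (z = 1.645). From Trial design: 1:1 allocation. From Trial status: 267 recruited by 2 June 2025, start dates 21 August and 19 September 2023, close by August 2025. I read 267 as young people (or parent–child pairs).

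**Formulas.** Intervention risk p = 1 − 0.673^HR, which is 0.2115 at HR 0.60 (the protocol prints 0.211) and 0.1989 at HR 0.56. Expected events E = N × 0.9 × (0.327 + p)/2. Power by Schoenfeld is Φ(√E × |ln HR|/2 − 1.645), and by Freedman Φ(√E × (1 − HR)/(1 + HR) − 1.645).

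**Reproducing the stated figures, N = 400.** At HR 0.60, E = 360 × 0.2693 = 96.9 and √E = 9.845.
- Schoenfeld: Φ(9.845 × 0.2554 − 1.645) = Φ(0.870) = 80.8%.
- Freedman: Φ(9.845 × 0.25 − 1.645) = Φ(0.816) = 79.3%.

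These bracket the printed 79.9%. At HR 0.56, E = 94.7 and the two methods give 88.0% and 86.4%, which bracket the printed 87.0%. The printed powers are therefore right for 400 randomised.

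**Accrual.**
- From recruitment start: 267 in 651 days, or 12.5 per month.
- From first consent: 267 in 622 days, or 13.1 per month.
- By 1 August 2025 (60 more days): 292 or 293.
- By 31 August 2025 (90 more days): 304 or 306.
- Needed for 400: 400 − 267 = 133 more. That is 133/(90/30.44) = 45 per month to 31 August, about 3.5 times the average so far, or 67 per month to 1 August.
- If the rate doubled from 2 June to 31 August: 341–344, taken as about 345.

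**Power at those numbers** (Freedman to Schoenfeld, same one-sided test):

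| N randomised | Events, HR 0.60 | Power, HR 0.60 | Power, HR 0.56 |
|---|---|---|---|
| 400 | 96.9 | 79.3–80.8% | 86.4–88.0% |
| 345 | 83.6 | 73.9–75.5% | 81.7–83.5% |
| 305 | 73.9 | 69.3–70.9% | 77.4–79.3% |
| 292 | 70.8 | 67.7–69.3% | 75.8–77.8% |

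One participant more or fewer than 305 moves power by only about 0.1 point.

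**The case against.** The strongest reply is that no printed figure is wrong. The power statement is conditional on 400, it reproduces, and its wording marks 400 as a ceiling. Trial status is a dated snapshot, and recruiting behind target is a matter of conduct that the management group and steering committee already monitor. All of that is true. But the section also states 400 as the aim and gives no power below it. Trial status states a forward plan as well as a count. Oversight is the route for resolving the gap; it does not resolve it in the text.

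A second reply is that a flat average includes start-up and the period before the inclusion criteria were broadened, when only 20 had consented, so recent accrual may be faster. This stands as a limit on precision: the article gives no recent rate, and 292–306 is not a documented number. It does not rescue 400, since doubling the rate still leaves about 345.

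A third reply is that the result will be reported as an HR with a 95% CI, which shows the precision achieved whatever power was planned. That reduces the harm but does not make the stated power match the timetable.

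Three stronger readings are tempting, and the documents do not support them:
- **That about 305 is an upper bound on the number randomised.** This would need 267 to be a count at consent, with losses during PTO and no acceleration. The article says only recruited, does not define it, and gives no figure for loss before randomisation.
- **That the written timetable overruns February 2027.** On the written dates it does not: 31 August 2025 plus 12 weeks plus 9 months is about August 2026. A clash can arise only if recruitment runs on to 400 at the old rate. That would be reached in April 2026, with last outcomes between January 2027 (no PTO) and April 2027 (full PTO).
- **That the calculation for 400 should be struck out.** It is the a priori rationale and is correct on its own terms.

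**Conclusion.** The point holds as a mismatch between the stated size and power and the article's own recruitment plan, not as an arithmetic error. At the average rate to date, the expected total is about 292–306 and power is about 68–71% at HR 0.60, roughly 10 points below the stated 79.9%. At HR 0.56 it is about 76–79% against 87.0%. With a doubled rate, power at HR 0.60 is still only about 74–76%.

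This rests on three assumptions: constant accrual to a close between 1 and 31 August 2025; everyone counted as recruited being randomised; and the protocol's own event risks, 10% attrition and one-sided test. The size of the shortfall is uncertain; that there is one, on the written dates, is not in serious doubt.

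**What to change.** Keep the calculation for 400 in the Sample size section as the design rationale. Beside it, state the expected number randomised and the power it gives at HR 0.60 and HR 0.56 on the same test. Replace that projection with the actual number randomised when recruitment closes, before unblinding.

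If 400 is still the target, change the August 2025 close and the later dates in Trial status to ones that recruitment, PTO and 9 months of follow-up can meet.

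In either case, state whether 267 counts consented or randomised young people, and track progress against 400 at randomisation.

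The first option costs a few sentences and a less favourable stated power, with no extra participants. The second costs recruitment time and a later end date.
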